### Stopping rules

Due to lack of report on pharmacopuncture safety, researchers and clinicians convened for discussion and review of inhouse safety records of pharmacopuncture patients for the past 4 years and existing literature on acupuncture safety [35] to assess potential adverse events which may require the participant to be dropped out from the study. Symptoms requiring early withdrawal from the study included local infection, severe progressive neurological disorders, nerve irritation/injuries, continued bleeding in area administered with acupuncture, and pneumothorax. The trial will be stopped if the principle investigator judges that there is unacceptable risk of SAEs.

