#### Post-treatment (8 weeks)

The primary endpoint will be at 5 weeks post-randomization, which marks the end of the 8 treatment sessions. Additional follow-up evaluations will be conducted after the primary endpoint. At the post-treatment phase, patients will be allowed pain medication intake, as needed, regardless of type or dose, and patterns of use will be investigated at each follow-up evaluation. To encourage attendance of follow-up evaluations and reduce number of drop-outs, all participants will have the choice to be provided with acupuncture and *Shinbaro* pharmacopuncture at the end of the trial phase (12 weeks post-randomization).

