#### Secondary acupuncture – acupuncture group

The secondary acupuncture physician will administer acupuncture at the acupoint marked by the initial physician in the acupuncture group, accessing the tissue perpendicularly at the marked area to a depth of 4 cm using a disposable sterile needle (40 mm × 0.4 mm; Dong-bang Acupuncture, SeongNam, Korea) without an acupuncture guide tube, and with no contact with the disinfected area. The physician will adopt a manner highly similar to *Shinbaro* pharmacopuncture in method, procedure and timing to maintain patient-blinding. The physician will also use needle twisting to evoke soreness similar to injection of solution, and inform the patient that solution injection may cause soreness. The physician will immediately remove the inserted needle while applying pressure to the surrounding tissue to reduce bleeding, and then apply pressure with dry sterilized gauze for about 15 seconds. A povidic saturated swabstick will be used for disinfection with gradually expanding circular strokes to about a 5 cm radius, and prevent wound infection with a Superpore wound dressing adhesive with the added effect of concealing the area from the physician who will remove the other needles.

Administration of secondary acupuncture (*Shinbaro* pharmacopuncture or acupuncture) will take place within the 20-minute initial acupuncture needle retention.

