### Sample size

There are no prior RCTs which have assessed the effect of *Shinbaro* pharmacopuncture in sciatic pain patients due to LDH. Therefore, the purpose of this pilot study is to calculate the sample size and assess the feasibility of a larger trial. A total of 60 participants with 20 patients per group will be recruited in light of the relatively short treatment and follow-up period. Factoring in a 20 % drop-out rate, we anticipate that this will be the minimum recommended number required for a pilot study [34].

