### Statistical analysis

The intention-to-treat and per-protocol analysis will be performed in all participants who complete the clinical trial with no major breach from the study protocol, and intention-to-treat will be the primary analysis. Missing values will be resolved using the last observation carried forward. Sociodemographic characteristics and treatment expectancy of study participants will be assessed by group. Continuous data will be presented as means and standard deviations, or medians and quartiles. One-way analysis of variance will be used if normally distributed, and Kruskal-Wallis test if not, and post-hoc analysis will be performed if there is a significant between-group difference. Categorical data will be expressed as frequencies and percents using chi-square test or Fisher’s exact test.

Analysis of covariance will be used to evaluate the primary outcome variable, VAS of sciatic pain at 5 weeks after randomization. Secondary outcome variables – VAS of LBP, NRS of sciatic pain, NRS of LBP, ODI, EQ-5D, and SF-36 -– will be assessed likewise. Between-group differences in PGIC and blinding assessment will use chi-squared tests.

Also, within-group differences before and after treatment (baseline and follow-up evaluations) will be examined using a paired *t* test or Wilcoxon signed rank test, and difference in time-by-treatment interactions using repeated measures analysis of variance. As an additional approach to quantify the difference among groups over total follow-up time, areas under the curve between the time of randomization and week 12 will be calculated and compared with 1-way analysis of variance.

All analyses will be performed using SAS version 9.1.3 statistical package (SAS Institute, Cary, NC, USA) with level of significance set at *p* < 0.05.

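### The stopping rule removes patients with listed adverse events from the study rather than only from treatment, so those withdrawn before week 5 have no observed primary VAS

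*Protocol article*

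**What the plan says.** The Stopping rules section of the protocol article describes a review meeting held to identify "potential adverse events which may require the participant to be dropped out from the study". It then gives the outcome as a requirement: "Symptoms requiring early withdrawal from the study included local infection, severe progressive neurological disorders, nerve irritation/injuries, continued bleeding in area administered with acupuncture", with pneumothorax as the last item. Both phrases refer to the study and neither refers to the assigned treatment. No other section says that such a patient goes on attending assessments.

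Three other parts of the article determine what follows:

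- **Timing.** Intervention (4 weeks) places the eight sessions in weeks 1 to 4. Post-treatment (8 weeks) sets the primary endpoint at week 5 after randomization. Table 1 schedules VAS at visits 2, 4, 6 and 8 (weeks 1, 2, 3 and 4) and then at weeks 5, 7, 9 and 12.
- **Analysis.** Statistical analysis names intention-to-treat as primary, but says that both the intention-to-treat and the per-protocol analyses cover "all participants who complete the clinical trial with no major breach from the study protocol". It adds: "Missing values will be resolved using the last observation carried forward".
- **Retention.** Post-treatment (8 weeks) offers all participants the needle treatments at week 12, with the stated aim: "To encourage attendance of follow-up evaluations and reduce number of drop-outs".

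**The concern.** A rule that protects patients needs to stop the treatment that may be harming them. It does not need to stop measurement. As worded, this rule does both, and so creates missing values in the primary outcome by design.

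Those values are unlikely to be missing at random. Continued bleeding at the needled area can by definition occur only in needled patients, and pneumothorax and local infection realistically arise mainly there too. Usual care consists of medication and physical therapy. Nerve irritation or injury and progressive neurological disorder can occur in any arm, but they bear directly on sciatic pain. Withdrawal can therefore depend both on arm and on the outcome being measured.

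Two of the trial's aims are also affected. The Stopping rules section itself notes how little is reported on pharmacopuncture safety, yet the rule makes no provision for later safety visits, blood tests (weeks 5 and 12) or MRI (week 12) in the patients whose recovery is of most interest. The pilot is also meant to inform the size of a larger trial (Sample size section), and drop-outs created by the rule would add to the attrition it observes.

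**Working it through.** The plan gives no figure on this point to reproduce. The check has three parts: what happens to a withdrawn patient, which comparisons are affected, and how far an arm mean could move.

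**1. What happens to a patient withdrawn in weeks 1 to 4**

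No week-5 VAS is observed. The Statistical analysis section allows two readings:

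- *Last observation carried forward.* The substitute comes from visit 2, 4, 6 or 8. By Table 1's week labels its age at the endpoint is 5 − 4 = 1 week to 5 − 1 = 4 weeks. Visit 2 is also the randomization visit and no VAS is scheduled at screening, so a patient withdrawn in week 1 contributes what is in effect the baseline value.
- *Completers only.* Taken literally, the wording excludes the patient even from the intention-to-treat analysis.

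Withdrawals after week 5 do not affect the primary endpoint.

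**2. Which comparisons are affected**

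The acupuncture arm is treated by "accessing the tissue perpendicularly at the marked area to a depth of 4 cm using a disposable sterile needle", and the pharmacopuncture arm is needled to the same 4 cm depth at the marked point. The needle-related triggers therefore bear mainly on the two comparisons with usual care, and less on pharmacopuncture against acupuncture.

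**3. Size**

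Input from the Sample size section: "A total of 60 participants with 20 patients per group will be recruited". One patient is 1/20 = 5% of an arm.

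- *Carried forward.* Let d be the true week-5 value minus the carried value. The arm mean is wrong by d/20.
- *Excluded.* Let m be the mean of the other 19 and d the patient's true value minus m. The full-arm mean minus the completers' mean is (19m + m + d)/20 − m = d/20.

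The documents give no value for d. The range below is an assumption.

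| Assumed d | Shift of arm mean, one patient (d/20) |
|---|---|
| ±10 mm | ±0.5 mm |
| ±20 mm | ±1.0 mm |
| ±30 mm | ±1.5 mm |
| ±40 mm | ±2.0 mm |

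If k patients in an arm have the same d, the shift is k × d/20. As an outer reference, the 20% drop-out allowance is 0.20 × 20 = 4 patients per arm. Four patients with d of 10 to 40 mm would move the mean by 4 × 10/20 = 2 mm to 4 × 40/20 = 8 mm. Nothing in the documents suggests that this rule alone would remove four.

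The documents give no event rate either. For assumed rates p of a listed event before week 5, the chance of at least one such withdrawal among the 40 needle-arm patients is 1 − (1 − p)^40:

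| Assumed p | Chance of at least one in 40 | Expected number (40p) |
|---|---|---|
| 1% | 33% | 0.4 |
| 2% | 55% | 0.8 |
| 5% | 87% | 2 |
| 10% | 98.5% | 4 |

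**The case against.** The strongest reply is that this is a condensed article. It never says that assessments cease, and procedures after withdrawal, such as a termination visit or safety follow-up, are usually set out in the full protocol. That would be an answer if the article were silent. It is not: it states the rule and words it as leaving the study. A site following this text would end follow-up. If the sponsor meant only that treatment stops, the same correction is needed. The full protocol may still soften the rule in practice.

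The first of the two phrases is weaker than the second. It says only that the events may require drop-out, so the requirement rests on one sentence.

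It can also be said that carrying values forward and the completers wording are weaknesses of the analysis section that would apply to any drop-out. That is so. What belongs to the stopping rule is the additional missing data, linked to arm and to outcome, and the number of such cases cannot be estimated from the documents.

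The age range for the carried value depends on Table 1's week labels. Counted from randomization at visit 2 to an endpoint five weeks later, the oldest value would be five weeks old rather than four. This does not change the argument.

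Finally, the effect is small per patient, its direction is unknown, the trial is a pilot, and the triggering event is still recorded and counted (Adverse events; Safety monitoring). These points stand. They limit the weight of the concern without removing it.

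**Conclusion.** The concern holds. Followed as written, the rule leaves any patient withdrawn during treatment without an observed primary outcome, and the analysis then uses a stale value or none.

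The effect is modest: 0.5 to 2.0 mm on an arm mean per affected patient, assuming a gap of 10 to 40 mm, and more if several patients in one arm are withdrawn. The direction is not determined. A near-baseline value carried forward could penalise a needle arm, while a value recorded before worsening could favour it. The comparisons with usual care are the more exposed. Confidence is medium, because the number of affected patients rests on assumed rates and the full protocol is not shown. The change is worth making because it costs little and also preserves safety follow-up.

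**What to change.** Keep the sponsor's list of triggering symptoms, but reword the Stopping rules section so that these symptoms require permanent discontinuation of the assigned study treatment and not withdrawal from the study. State that the outcome and safety assessments at weeks 5, 7, 9 and 12 continue as scheduled unless the patient withdraws consent. In the Statistical analysis section, state that the observed week-5 VAS of these patients enters the primary intention-to-treat analysis in the arm to which they were randomized.

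The cost is a change of wording and at most four already scheduled visits per affected patient. The downside is that some observed values will follow other care. Recording that care at each visit allows it to be reported alongside the result.

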### Ethics

This study has received approval from the Institutional Review Boards of Jaseng Hospital of Korean medicine in Korea (reference number KNJSIRB2015-08), and all investigators will adhere to the Helsinki declaration and Korean Good Clinical Practice guidelines, and receive three educational sessions on the protocol and SOP.

## Discussion

The purpose of this study is to assess the efficacy and safety of *Shinbaro* pharmacopuncture, which is included in LDH clinical practice guidelines, in severe non-acute sciatic pain patients with LDH. We will evaluate the specific mechanical and chemical effect of pharmacopuncture minus the mechanical effect of acupuncture at acupoints through comparison of pharmacopuncture and acupuncture. This study is also a practical comparative study comparing acupuncture, pharmacopuncture, and usual care, which are the most frequently used treatments for LDH in Korea.

Though clinical guidelines on LDH issued by the Health Council of the Netherlands [36] and the North American Spine Society [37] support use of conservative treatment as first-line treatment in absence of cauda equina syndrome, the efficacy of many conservative treatments for LDH remains unclear [38]. For determination of the contents of the usual care group for LDH in our study, we referred to several clinical guidelines and systemic reviews, but found conflicting evidence on the efficacy of various conservative treatments. While US national guidelines recommend epidural steroid injections for short term (2–4 weeks) pain relief, a report from the Korean National Evidence-based Healthcare Collaborating Agency analyzing the results of systemic reviews and National Health Insurance reimbursement claims states that evidence to make a recommendation for use of epidural steroid injections for pain or functional recovery is weak [39]. Also, evidence for or against other pharmacological and non-pharmacological treatments including non-steroidal anti-inflammatory drugs (NSAIDS), muscle relaxants, antidepressants, physical therapy, traction, and exercise was mostly insufficient or against use. We therefore decided to apply interventions most frequently used in actual clinical practice in Korea in selecting usual care group treatment rather than follow evidence-based guidelines. Korea has a government-operated national health security system, based on a health insurance scheme that covers the entire population and all medical facilities. The system reimburses approved medical expenses of most diseases including LDH, and the HIRA service database contains information on medication and medical service use, and diagnoses. The HIRA database is, therefore, a useful source of epidemiologic data and allows for nationwide population studies of various neurologic and non-neurologic diseases [40]. We summarized most frequently used treatments in patients with a primary diagnosis of LDH (KCD: M51, M541) in the 2011 HIRA National Patients Sample for physician reference in the usual care group in an effort to establish a rational and legitimate method of usual care.

The effect of pharmacopuncture is believed to be produced through a combined effect of placebo, needle stimulation, and the mechanical and chemical effect of the solution. We reasoned that evaluation of the specific effect of pharmacopuncture against the non-specific effect of acupuncture (placebo effect and needle stimulation effect) at matching acupoints would validate pharmacopuncture use as distinct from acupuncture. As acupuncture points and needle-type hold relevance in determining effect, we will assign acupoint selection for *Shinbaro* pharmacopuncture and acupuncture to the blinded initial acupuncture physician and administer acupuncture perpendicularly at the acupoint with an acupuncture needle of the same shape and size as *Shinbaro* pharmacopuncture needles. To strengthen blinding and induce a homogeneous placebo effect in groups, the second physician will evoke a sensation similar to that of pharmacopuncture stimulation by twirling the acupuncture needle and refrain from exposing any factors that may inform the patient of the method of treatment (e.g. advice, precautionary measures, disposal of used products) in accordance with the protocol and prior education and training.

Limitations of our study include that recruiting at a mainly Korean medicine-based hospital may lead participants to have higher expectations for pharmacopuncture or acupuncture than conventional treatment due to the cultural and medical environment of Korea. We will attempt to assess the effects through Credibility and Expectancy Questionnaires, and will discuss the results in the results paper.

GCSB-5, which is the primary ingredient of *Shinbaro* pharmacopuncture, has a long history of clinical use for spinal disorders such as LDH in Asia, and recent interest in natural products has led to pharmacological studies on its effects, showing that GCSB-5 modulates acute and chronic inflammatory processes, [41] has neuroprotective, nerve regeneration promoting and motor functional recovery accelerating properties by reducing oxidative stress, [42] and articular cartilage protective effects against progression of osteoarthritis [43]. Based on clinical experience and experimental evidence, GCSB-5 was developed as a pharmaceutical following prescription drug development standards and approved as a natural product for treatment of osteoarthritis by the Korean Food and Drug Administration in January 2011, [44–47] consequently providing evidence for clinical use in the form of pharmacopuncture. Analyses of outpatient data at 12 branches of a spine-specialty network Korean medicine hospital from December 2010 to October 2014 revealed that 289,860 patients (77.6 %) received pharmacopuncture an average 8.2 ± 12.3 times out of 373,755 outpatients, and of these, 104,445 (36 %) received *Shinbaro* pharmacopuncture, ranking second after bee venom pharmacopuncture. A 2010 survey on clinicians with at least 5 years’ experience of pharmacopuncture reported that 38 % used it to treat musculoskeletal patients to a depth of 15 mm using 1 cc or less [48].

Most pharmacopuncture studies are currently being conducted in Korea and China, and the majority are on bee venom pharmacopuncture. One clinical trial conducted in China reported that in treatment of LDH patients of blood-stasis type using *Gegensu Zhusheye* (puerarin pharmacopuncture), electroacupuncture and blood-letting cupping, using *Hyeopcheok* (*Huatuo Jiaji*, EX B2) points showed better improvement than that of *Ashi* points in symptom and pain relief, interleukin-6 levels and hemodynamics, [49] but the study was designed to differentiate the effect of different acupoints in the treatment group and control, and thus not well-equipped to observe the overall efficacy of pharmacopuncture. An analysis of the publication types of pharmacopuncture-related papers published in the journal “*The Acupuncture*,” registered in the National Research Foundation of Korea, showed that 438 pharmacopuncture-related papers were published up to August 2006, which takes up about 34.6 % of the total 1,268 papers published in the journal. Of these papers, 355 were non-clinical, 70 clinical, and 14 literature reviews, showing a large proportion of non-clinical papers [50]. The “*Journal of Pharmacopuncture*,” also registered in the National Research Foundation of Korea, has published 196 papers (73.9 %) on pharmacopuncture out of 265 manuscripts published up to June 2006 since its foundation in 1997, and though the percentage of clinical studies was higher at 35 % (67 papers), clinical study papers on pharmacopuncture in both journals were generally limited to observational studies and case series. The most frequently studied type of pharmacopuncture was bee venom pharmacopuncture in both journals, [51] illustrating the need for more clinical studies on different types of pharmacopuncture.

*Hyeopcheok* points are situated at or in close proximity to the nerve roots, and stimulation of this area is comparable to nerve root blocking therapy commonly used in conventional treatment for LDH. It can be surmised that the reason why *Hyeopcheok* points, in addition to regular meridian acupuncture points, has a long history of use in spinal disorders was at least partly due to a need to stimulate surrounding deep tissue and the nerve root that was being irritated from protruded disc tissue. While the current study aims to assess whether using pharmacopuncture is more effective at *Hyeopcheok* points than regular acupuncture, we will consider further comparisons with nerve root blocking therapy using steroidal injections. Comparative effect studies on bee venom pharmacopuncture, which has been rigorously studied and is widely used in Asia, should also be given due consideration.

While regulations for post-marketing surveillance of medicine and medical supplies do not apply to pharmacopuncture products, agreements to the aim of regulatory standard enforcement in products not obligated to receive post-marketing surveillance in pharmaceutical affairs laws have been reached by the Korean Food and Drug Administration and Ministry of Health and Welfare. Despite the fact that over 200 types of herbal medicine injections are available from pharmaceutical companies in China [52] and the market is fast growing in Korea also, with pharmacopuncture recognized in private insurance sectors such as car insurance, rigorous pharmacopuncture trials utilizing appropriate controls (placebo or active), randomization and blinding are scarce. This trial will evaluate the comparative clinical effectiveness of deep pharmacopuncture for severe non-acute sciatic pain patients diagnosed with LDH with the usual care of conventional medicine and that of Korean medicine (acupuncture), and apply randomization and group allocation concealment, with physician, patient, and outcome assessor-blinding to effectively remove bias. This study will be the first well-designed rigorous RCT to assess the comparative effectiveness of pharmacopuncture in accordance with Consolidated Standards of Reporting Trials (CONSORT) and Standards for Reporting Interventions in Clinical Trials of Acupuncture (STRICTA) guidelines, monitor its safety, and serve as the basis of a large-scale, multicenter trial.

